## Abstract

**Background:**

Hepatitis C virus infection is highly prevalent among people who inject drugs. Opioid substitution therapy, the standard treatment for opioid dependence, provides an excellent opportunity for the treatment of hepatitis C virus infection due to the close and regular contact between patients and clinicians. However, there is little research on the impact of opioid substitution therapy on the prevalence of the hepatitis C virus at a national level. This paper describes the protocol for the Epidemiology of Hepatitis C Virus Infection among People Receiving Opioid Substitution Therapy (ECHO) study. The aim of this study is to estimate the national prevalence and incidence of hepatitis C virus infection among people receiving opioid substitution therapy in Germany and to describe factors associated with hepatitis C treatment uptake and seroconversion.

**Methods/Design:**

An observational, longitudinal, multicentre study is being conducted between 2014 and 2016 in a representative sample of approximately 2500 people receiving opioid substitution therapy from about 100 clinicians providing opioid substitution therapy in Germany. Data will be collected during routine patient care and by means of patient and clinician questionnaires at baseline and 12-month follow-up. Stratified sampling will be performed to obtain a representative sample of clinicians providing opioid substitution therapy. The strata will be constructed based on the distribution of the total sample of clinicians providing opioid substitution therapy in Germany according to German Federal State and the number of patients per clinician.

**Discussion:**

Opioid substitution therapy may be an important strategy to prevent the spread of hepatitis C virus in opioid dependent populations, but its effectiveness may be diminished by our limited understanding of factors associated with treatment uptake and seroconversion. The present study will provide important information for developing strategies to address hepatitis C virus-related disease burden in people receiving opioid substitution therapy.

**Trial registration:**

ClinicalTrials.gov: NCT02395198

## Background

Injecting drug use is the primary mode of transmission for hepatitis C virus (HCV) infection in developed countries [1–3] and accounts for the vast majority of new infections [4, 5]. With up to 90 % of people who inject drugs (PWID) being HCV-antibody-positive, HCV is highly prevalent in this target group. Worldwide, 6–15 million drug users are infected with the virus [6]. Opioid substitution therapy (OST), the standard treatment for opioid dependence, provides an excellent opportunity for managing HCV infection due to the close and regular contact between patients and clinicians. However, there is little research on the impact of OST on HCV prevalence and incidence at a national level.

HCV infection is characterized by an asymptomatic onset and progression, which delays early diagnosis and therefore treatment. Treating the infection in its early stages is vital to avoiding long-term complications. Approximately 15 % of chronic HCV-infected PWID develop liver cirrhosis within 20 years [7] and the burden of HCV-related morbidity and mortality among PWID is significant and increasing [8–10]. Infection duration is a risk factor for accelerated liver disease progression [1] and the stage of liver disease is, in turn, a predictor for the success of antiviral treatment [11, 12]. Early diagnosis of HCV infection is therefore of utmost importance.

Accordingly, the current guidelines of the Association of the Scientific Medical Societies in Germany (AWMF) for the prevention, diagnosis and treatment of HCV infections recommends testing former and active drug users every 12 months [13]. OST provides optimal conditions for regularly testing and monitoring HCV infections by virtue of the therapeutic relationship and routine contact between patients and clinicians. Nevertheless, recent data from a convenience sample of nearly 600 OST clinicians in Germany demonstrated limited implementation of the AMWF guidelines, particularly in small OST centres, with only two-thirds of the centres regularly testing patients’ HCV status [14].

In 2011–2012, HCV antibody levels among national samples of PWID in Europe varied from 19 to 84 %, with 7 of 11 countries reporting prevalence rates higher than 50 % [15]. Although no national data is available for Germany, subnational coverage in 2011 suggests a high prevalence of HCV, with 56 % of PWID in Berlin having ever been infected with HCV and 71.6 % in the city of Essen [16, 17]. Cohort studies provide some evidence for the effectiveness of OST in reducing HCV infections [18, 19]. Also model projections show that OST can reduce HCV prevalence if its coverage is increased sufficiently, however these reductions can be modest and require long-term coverage [20–22]. Real-life data on the effect of OST on HCV prevalence at a national level is lacking.

Despite growing evidence that PWID can successfully be treated for HCV [23], treatment uptake varies considerably between countries, from 0 to 64 % [24–26]. There are various barriers to HCV treatment initiation, including fears of low efficacy and adverse side effects among drug users, as well as concerns of low adherence and perceived risk of reinfection among clinicians [14, 27–29]. Yet our understanding of factors influencing HCV treatment uptake in OST is limited, as many of these studies have been conducted in populations of drug users rather than OST patients, using convenience samples and not representative national samples.

Moreover, the findings are based on the old HCV treatment regimen with interferon as opposed to newer treatments with direct-acting antivirals (DAA) without interferon. Concerns have been raised that drug users may become careless in safe injection practices if they are aware of the high success rate and few side effects of the new HCV therapy [30], thereby leading to higher reinfection rates. With the impending interferon-free era of HCV therapy, it is important to re-examine factors influencing treatment uptake and seroconversion to inform public health strategies.

The aim of the Epidemiology of Hepatitis C Virus Infection among People Receiving Opioid Substitution Therapy (ECHO) study is to estimate the national prevalence and incidence of HCV infection among OST patients in Germany and to examine factors associated with HCV treatment uptake and seroconversion.

## Methods/Design

### Study design

ECHO is a non-interventional, observational, longitudinal study being conducted between 2014 and 2016 in a large representative sample of approximately 2500 OST patients from about 100 OST clinicians across Germany. Data is collected during routine patient care and from questionnaires administered to patients and clinicians.

At baseline, we examine OST patients’ HCV status to assess HCV prevalence. Also the rate of HCV treatment uptake among OST patients and factors associated with treatment uptake are examined. Patients that are HCV negative at baseline or started HCV treatment up to 12 months prior to baseline are followed up after 12 months to assess the HCV incidence rate, factors influencing seroconversion, and (if applicable) the course of HCV treatment (e.g., treatment outcome, side effects). At both baseline and follow-up, the HCV status will be recorded from the participant’s chart. Clinicians are reminded of the HCV treatment guidelines in Germany, which recommend yearly HCV testing in this high-risk population, to encourage them to perform HCV antibody and/ or HCV RNA testing through the standard of care within the clinics. The study duration is either 1 day or 12 months depending on whether participants take part in the follow-up. Patient recruitment takes place over 12 months, data collection over 18 months, and the total length of the study is 27 months.

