#### Sample size

The sample size calculation is based on the primary outcome variable of HCV incidence among OST patients. The literature reports an HCV incidence of 2–4 per 100 person-years in this target group [32, 33]. For a sample size of (at least) 32 patients with HCV seroconversion and an observation period of 1 year, 800 HCV antibody-negative patients are needed as an initial sample size. Based on previous literature [34], we assume an HCV antibody prevalence of about 68 % among OST patients in Germany. Therefore a sample size of 2500 patients is needed (32 % corresponds to *N* = 800).

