##### *C. HCV diagnostic and treatment*

Patient’s most recent anti-HCV test and HCV-RNA test results (including viral load, HCV genotype(−subtype), and duration of chronic HCV infection) and dates of test results are recorded from the participant’s chart. Clinicians are reminded of the HCV treatment guidelines in Germany, which recommend yearly HCV testing in this high-risk population. Further, clinicians report patient’s past receipt of HCV treatment, treatment start and end date, treatment outcome and, if applicable, reasons for treatment termination.

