##### *C. Current HCV status*

The current HCV status is recorded from the participant’s chart. Clinicians are reminded of the HCV treatment guidelines in Germany, which recommend yearly HCV testing in this high-risk population.

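### The primary event is antibody seroconversion, but the plan's testing prompt accepts RNA alone and its follow-up cohort is not tied to antibody status, so incidence can be biased in either direction

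*Protocol article*

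**What the plan says.** **Outcome and cohort.** The Sample size section states: "The sample size calculation is based on the primary outcome variable of HCV incidence among OST patients". It sizes the study in terms of seroconversion: "For a sample size of (at least) 32 patients with HCV seroconversion and an observation period of 1 year", with "800 HCV antibody-negative patients are needed as an initial sample size". The Planned statistical analysis section likewise follows about 800 seronegative patients for 12 months.

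**Testing.** The Study design section takes HCV status from the chart at both time points. It says clinicians are reminded of the yearly testing guideline to encourage them "to perform HCV antibody and/ or HCV RNA testing through the standard of care". The same section defines the incidence part of the follow-up cohort only as patients who are *HCV negative* at baseline.

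**Records.** The baseline clinician questionnaire (C. HCV diagnostic and treatment) collects the patient's "most recent anti-HCV test and HCV-RNA test results", with dates. The follow-up questionnaire (C. Current HCV status) is summarised in two sentences. The first begins "The current HCV status is recorded from the participant" and gives the chart as the source; neither sentence names a test type or a date.

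**The concern.** In an antibody-negative patient, seroconversion is established by a later positive antibody test. RNA shows whether virus is present on the day of the test. The two differ in someone who was infected and cleared: antibody-positive, RNA-negative. The testing prompt and the cohort label both leave open which marker is meant, and this can go wrong in two ways.

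- **Too few events.** A seronegative patient infected and cleared within the year, and followed by RNA alone, can be read as a non-event while the full year stays in the person-time.
- **Too many events.** If the cohort is formed from the Study design wording, a patient already antibody-positive but RNA-negative can enter as negative. A later antibody test would then look like a new seroconversion.

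The choice of test depends on practice habit, so practice habit can also enter the planned analysis of factors associated with seroconversion. The first problem cannot be repaired afterwards if no antibody test was done. The second can be, where the baseline anti-HCV result is on file.

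**Working it through.** **Step 1: the plan's own figures.** The Sample size section says: "The literature reports an HCV incidence of 2–4 per 100 person-years in this target group". At the upper end, 800 × 0.04 × 1 year = 32 events. At the lower end, 800 × 0.02 = 16. With 68 % antibody prevalence, 800 / (1 − 0.68) = 2500. The stated figures reproduce, and the sample size is not in error on this point. The exact Poisson 95 % interval for 32 events in 800 person-years is 2.74 to 5.65 per 100.

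**Step 2: possible loss of events.** Let *f* be the share of follow-ups resting on RNA alone and *c* the share of new infections cleared before that test. The share of events missed is *f* × *c*. Neither input is in the documents; the ranges are assumptions.

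| *f* | *c* = 15 % | *c* = 25 % | *c* = 40 % |
|---|---|---|---|
| 0 % | 0 % | 0 % | 0 % |
| 10 % | 1.5 % | 2.5 % | 4.0 % |
| 30 % | 4.5 % | 7.5 % | 12.0 % |
| 50 % | 7.5 % | 12.5 % | 20.0 % |

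For *f* from 10 to 50 %, out of 32 events this is 32 × 0.015 = 0.5 up to 32 × 0.20 = 6.4. A true rate of 4.0 per 100 person-years would be estimated as 3.94 down to 3.20, and a true rate of 2.0 as 1.97 down to 1.60.

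**Step 3: possible gain of false events.** Let *m* antibody-positive, RNA-negative patients enter as negative and be antibody-tested at follow-up (*m* is an assumption). The estimated rate is (32 + *m*) / (800 + *m*):

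- *m* = 8: 40 / 808 = 4.95 per 100
- *m* = 16: 48 / 816 = 5.88 per 100

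**Step 4: which scoring rule repairs it.** Take 800 patients, a true rate of 4.0 per 100, *f* = 30 % and *c* = 25 %. Then 560 patients have an antibody result (560 × 0.04 = 22.4 events) and 240 have RNA only (9.6 true events, of which 7.2 are still RNA-positive).

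- Everyone kept, RNA-only negatives counted as non-events: (22.4 + 7.2) / 800 = 3.70 per 100.
- RNA-only positives counted, RNA-only negatives dropped: 29.6 / (560 + 7.2) = 29.6 / 567.2 = 5.22 per 100.
- All RNA-only follow-ups left out, positive and negative alike: 22.4 / 560 = 4.00 per 100.

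The second rule misses the true rate by more than the first. Only the third recovers it, provided that the choice of test is unrelated to infection risk.

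**The case against.** The strongest reply is that the sentence about testing is a guideline reminder in a non-interventional study and not an outcome rule. It also covers patients recently treated for HCV, for whom RNA is the natural test, so allowing either marker suits a mixed population. The Planned statistical analysis section speaks of RNA confirmation tests, which suggests antibody testing first. The Sample size and Planned statistical analysis sections fix the cohort as antibody-negative, so an antibody-positive, RNA-negative patient at follow-up would be a seroconverter on the plan's own terms. The article also condenses a questionnaire that is not shown.

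Much of this stands, and it rules out stronger readings that a reader might infer:

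- *The plan scores an RNA-only negative as no event, so incidence is biased low.* No section says this. The bias is possible, not stated, and the opposite direction is also open.
- *The follow-up form records only an undifferentiated status.* The article gives a summary; the full form may hold test type and date.
- *Current status means current viraemia for everyone, so 15–40 % of events are lost.* That reading runs against the antibody-based event and cohort in the Sample size and Planned statistical analysis sections.

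The reply does not remove the mismatch itself. The reminder is the plan's described means of prompting testing, and for seronegative patients it accepts a test that cannot show the primary event. The remark on RNA confirmation concerns the distribution of genotypes and subtypes and does not set the follow-up test. The Study design wording for the cohort is looser than the wording used for sizing and analysis.

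**Conclusion.** The point holds as a mismatch between the stated event and the stated testing prompt and cohort label. It does not establish a bias of known sign or size. The downward loss is 1.5–20 % of events under the assumed shares, and zero wherever antibody is tested. Even the upper figure (3.2 instead of 4.0 per 100) lies within the sampling interval from 32 events, but unlike sampling error it would not shrink with more patients. The upward error depends on an unknown number of misclassified entrants and arises only if the Study design wording, and not the seronegative definition in the analysis section, governs who is counted. The change should be made because it is cheap and because a missing antibody result cannot be recovered at analysis.

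**What to change.** 1. In the Study design section, replace *HCV negative* by antibody-negative for the incidence cohort, to match the Sample size section.
2. In the existing reminder, name anti-HCV as the outcome test for patients who were antibody-negative at baseline.
3. Make sure the follow-up record holds dated anti-HCV and HCV-RNA results, as the baseline questionnaire does. If the full form already has these fields, the article need only say so.
4. Define the event as anti-HCV negative at baseline and anti-HCV positive at follow-up.
5. Restrict the primary incidence estimate to patients with an anti-HCV result at follow-up. Report all RNA-only follow-ups, positive and negative alike, separately or in a sensitivity analysis. Do not count the positives while dropping the negatives.

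**Cost.** Items 1 to 4 are wording of the form, reminder and definition. Item 5 costs precision by an amount that depends on the unknown RNA-only share. At 4 per 100, a 10 % share leaves 720 patients and 28.8 expected events; a 50 % share leaves 400 and 16. The relative standard error, 1/√events, goes from 17.7 % (32 events) to 18.6 % or 25 %. The restricted estimate also assumes that the choice of test is unrelated to infection risk; comparing baseline characteristics of RNA-only and antibody-tested patients would help to judge this.

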### Participants

#### Eligibility criteria

Study participants include patients and their clinicians. Clinicians are recruited first and must:Meet the minimum qualification requirements for addiction therapy in accordance with the Ordinance on the Prescription, Dispensing and Proof of the Disposition of Narcotic Drugs (BtMVV) as defined by the Chamber of PhysiciansCurrently provide OST to 4 or more patientsHave provided written informed consent

Patients recruited from the consenting clinicians must meet the following criteria:Diagnosed opioid dependence according to the International Statistical Classification of Diseases and Related Health Problems, 10^th^ revision (ICD-10; [31])Currently in OSTMinimum age 18No severe mental impairmentSufficient German reading and writing skillsWritten informed consent

In Germany, clinicians that do not meet the requirements for addiction therapy in accordance with the BtMVV are allowed to provide OST to a maximum of three patients under the supervision of a clinician (consultant) meeting the minimum qualification requirements for addiction therapy. We exclude all clinicians with less than four OST patients to ensure that only clinicians with a qualification for addiction therapy are included in the study.

#### Sample size

The sample size calculation is based on the primary outcome variable of HCV incidence among OST patients. The literature reports an HCV incidence of 2–4 per 100 person-years in this target group [32, 33]. For a sample size of (at least) 32 patients with HCV seroconversion and an observation period of 1 year, 800 HCV antibody-negative patients are needed as an initial sample size. Based on previous literature [34], we assume an HCV antibody prevalence of about 68 % among OST patients in Germany. Therefore a sample size of 2500 patients is needed (32 % corresponds to *N* = 800).

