Beyond our main research questions, we will examine a range of covariates and associated topics, such as QOL and shared decision-making. QOL is increasingly acknowledged as an important treatment outcome criterion in OST. Yet most studies merely measure QOL at the beginning of OST. The ECHO study will be the first to deliver cross-sectional, representative data on the QOL for an entire population of patients in OST. Furthermore, patient-centred care is recognized as a measure to improve health care by empowering patients to be actively involved in their treatment. Yet this approach is not applied in OST. ECHO will be one of the first studies to explore OST patients’ preferences in shared decision-making, satisfaction in patient care, and needs and attitudes concerning treatment.

The present study appears feasible, as we have been able to draw a clinician sample according to the representativeness criteria GFS and PPC up until manuscript submission, and our monitoring framework appears effective. While questionnaires are occasionally incomplete, the implemented monitoring system is efficient and ensures complete data sets. We hope this is encouraging to researchers in other countries to pursue similar investigations.

The study has some anticipated limitations. The sample may be subject to selection bias, as only 319 of 2691 OST clinicians were willing and eligible to take part in the ECHO study and clinicians have been dropping out of the study since. Particularly clinicians from small practices seem unwilling to participate in the present study. A similar pattern was observed in a study in which clinicians from small OST centres did not regularly test for HCV infection in patients [14]. The representability of the sample may be compromised if too many clinicians drop out.

Further, the sample size calculation assumes a 1-year follow-up of all individuals and does not consider potential dropouts. Incidence estimates may be biased if only a small sub-sample returns for follow up. However, Germany has one of the highest retention rates of OST in the world [43]. The present study will provide first insights into HCV incidence among OST patients. All potential limitations will be discussed in following publications.

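### The (at least) 32 seroconversions behind the sample size are the most that 800 antibody-negative patients can be expected to give under the cited incidence range, not the least

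*Protocol article*

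**What the plan says.** In the protocol article, Methods/Design, Participants, Sample size, the study is sized on incidence: "The sample size calculation is based on the primary outcome variable of HCV incidence among OST patients". The rate is given as a range: "The literature reports an HCV incidence of 2–4 per 100 person-years in this target group". The event count follows, "For a sample size of (at least) 32 patients with HCV seroconversion and an observation period of 1 year", and from it the at-risk cohort: "800 HCV antibody-negative patients are needed as an initial sample size". The total comes from the assumed prevalence, "we assume an HCV antibody prevalence of about 68 % among OST patients in Germany", which leaves 32% at risk: "Therefore a sample size of 2500 patients is needed". The section does not say which rate within the range was used, and it states no power or precision target.

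Planned statistical analysis repeats the expectation of about 800 seronegative patients observed for 12 months. The limitations part of the Discussion admits that "the sample size calculation assumes a 1-year follow-up of all individuals and does not consider potential dropouts".

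**The concern.** The range and the event count do not fit together. If incidence may lie anywhere from 2 to 4 per 100 person-years, a count described as a minimum should follow from the lower end. It appears to follow from the upper end, and with no losses.

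The event count is the only justification given for 2500 patients. It also tells readers how much information to expect for the incidence rate and for the bivariate and multivariate analyses of factors associated with seroconversion in Planned statistical analysis. An analyst who expects at least 32 events could choose more candidate factors than half that number would support.

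Complete retesting is not secured by the design either. Under Study design, HCV status is read from the chart and clinicians are only reminded of the yearly-testing guideline. The Background reports a survey in which only two-thirds of OST centres tested regularly. That survey was a convenience sample of centres and gives no patient-level retest rate, but it does not support assuming that everyone is retested.

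**Working it through.** **Inputs, all from the protocol article.** Incidence 2–4 per 100 person-years, 32 seroconversions, 1 year of observation, 800 antibody-negative patients, antibody prevalence 68%, total 2500 (Sample size); no allowance for dropout (Discussion).

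**Formulas.** Expected events = number at risk × rate × 1 year. Number at risk needed = 32 / rate. Total needed = number at risk / (1 − 0.68).

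**Reproducing the plan's figures.** At 4 per 100: 32 / 0.04 = 800 and 800 / 0.32 = 2500. Both are exact, so the plan used 4 per 100 with complete follow-up. At 3 per 100 the number at risk would be 32 / 0.03 = 1067, and at 2 per 100 it would be 32 / 0.02 = 1600. Neither gives 800.

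**What 800 person-years yield over the cited range, with no losses.** The exact 95% limits for x events are χ²(0.025; 2x)/2 and χ²(0.975; 2x + 2)/2, each divided by 800 person-years.

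| Rate per 100 person-years | Expected events | Exact 95% CI for the rate if that count is observed | Poisson P(32 or more events) | At risk (total) needed to expect 32 |
|---|---|---|---|---|
| 2 | 800 × 0.02 = 16 | 1.1–3.2 | 0.0003 | 1600 (5000) |
| 3 | 800 × 0.03 = 24 | 1.9–4.5 | 0.07 | 1067 (about 3334) |
| 4 | 800 × 0.04 = 32 | 2.7–5.6 | 0.52 | 800 (2500) |

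Converting the rate to a one-year risk, 1 − exp(−rate), changes little: 15.8, 23.6 and 31.4 expected events.

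**Effect of loss or missing retests.** The documents give no loss rate, so 10–30% is an assumption. If such patients contribute no data, expected events are 800 × (1 − loss) × rate:

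- 10%: 14.4 at 2 per 100 to 28.8 at 4 per 100
- 20%: 12.8 to 25.6
- 30%: 11.2 to 22.4

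If lost patients contribute half a year on average, 20% loss leaves 800 × 0.9 = 720 person-years and 14.4 to 28.8 events. In every case the count at 4 per 100 is below 32.

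**The case against.** The best defence is that the sentence sets a requirement and is not a forecast: 32 is a target, 800 is the number needed to reach it, and words such as *at least* are normal for a target. On that reading no sum is wrong, since 32 → 800 → 2500 is exact. This does not rescue the paragraph. As a requirement, 800 is the smallest cohort that could suffice anywhere in the cited range, and it falls short at every lower rate.

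Several other points do stand:

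- The missing dropout allowance is openly disclosed in the Discussion. What is not disclosed is the use of the top of the incidence range, and that alone halves the expected count at 2 per 100.
- 32 is a maximum for the expected count, not a cap on the count observed.
- The 20% loss is an assumption of this review. On the protocol's own inputs the lowest expected count is 16, exactly half of 32.
- Incidence is estimated, not tested, so no planned decision hinges on reaching 32. The interval at 16 events is narrower in absolute terms (3.2 − 1.1 = 2.1) than at 32 (5.6 − 2.7 = 2.9). Relative to the rate it is wider: 2.1/2 = 1.05 against 2.9/4 = 0.73.
- The Poisson intervals treat patients as independent, although they are sampled within 88 clinicians, up to 60 from each. Clustering could make the true intervals wider.

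A reason for choosing 4 per 100 might lie in the cited literature or the full protocol. That would explain the choice, but the paragraph would still present the most favourable case in its own range as a minimum.

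**Conclusion.** The concern holds. On the protocol's own inputs, 800 antibody-negative patients with complete one-year follow-up are expected to give 16–32 seroconversions. The stated minimum is the upper end of that range, and it is reached or exceeded with probability 0.03%, 7% or 52% at 2, 3 or 4 per 100 person-years. With an assumed 20% lost or not retested and contributing no data, the expected range is about 13–26.

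This rests on the 68% prevalence being right, on incidence lying within the cited range, and on Poisson counts with independent patients. An incidence above 4 per 100 would give more events, but the document offers no basis for one. The flaw lies in the stated justification of the study size for the primary outcome. It does not show that 2500 patients is the wrong number.

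**What to change.** Keep 2500 and restate the Sample size paragraph:

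- Delete the words in parentheses before 32, and say that 32 corresponds to 4 per 100 person-years with complete follow-up.
- State that 800 antibody-negative patients are expected to give about 16–32 seroconversions over 12 months if all are followed and retested, and about 13–26 if 20% are not (label the 20% as an assumption).
- Give the precision this implies as exact Poisson 95% confidence intervals: about 1.1–3.2 per 100 person-years at a rate of 2 and 2.7–5.6 at a rate of 4 with no losses. Add that these are wider with losses and ignore clustering within clinicians.

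Once 32 is no longer a minimum, this precision becomes the stated basis for 2500, and the text should say so plainly. If the sponsor does need 32 expected events over the whole cited range, rewording is not enough: at 2 per 100 that takes 1600 antibody-negative patients, or 5000 in total, before any loss.

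The cost is one reworded paragraph and a less favourable stated event count. No extra patients are needed and conduct does not change.
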